### Randomization and blinding

Computer-generated assignment at the patient level is used for randomization. Patients who are eligible, and have given informed consent, are randomized to either usual care or to the protocol for guided anesthesia according to the EEG. A one to one ratio of randomization of the patients between usual care and the protocol for EEG-guidance is used. Within the research team, members are trained to enroll participants and assign the randomization between the usual care or the protocol for EEG-guidance. Anesthesiologists and their team learn of the group assignment after the patient is brought into the operating room; an opaque, sequentially numbered, sealed envelope is opened to reveal the study group. The randomization sequence is generated by the data analysis center. The anesthesiologist and the team caring for the patient intraoperatively are not blinded to the group assignment. The patients and family members are not aware of the group assignment. The research team members who are in charge of the assessment of delirium postoperatively remain blinded to the group assignment. Chart reviews are conducted by individuals blinded to the group assignment and blinded to the outcome of the postoperative delirium assessments
^
29,
30
^. Predictability of the randomization sequence is minimized by recording in a separate document, unavailable to the members of the research team who enroll participants and assign groups, the details of patients who have already been randomized.

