^. EEG index values less than manufactures’ recommendations (BIS and WAVcns values less than 40 or a PSi less than 25) indicate a second trigger for decreasing the administration of anesthetic agents. It is important to remember that the protocol of guidance of anesthesia according to the EEG waveform is suggestive and not prescriptive. Clinical judgment can inform deviations from the protocol according to the specific situations encountered. For all patients, regardless of the allocation group, the low volatile alarm (0.3 minimum alveolar concentration or clinician’s discretion) sounds to decrease the risk of intraoperative awareness. In the usual care group, the EEG monitor values are masked from the anesthesia team, except for the signal quality measures, and the data are stored for analysis of epochs of EEG suppression. For sites using the BIS monitors and NeuroSENSE
^
**®**
^ monitors, anesthesiologists see the signal quality index (SQI) only and for sites using the SedLine
^
**®**
^ monitor practitioners only see the impedance quality of the electrodes.

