^. Patients will be assessed based on their randomization group in accordance with an intention-to-treat approach. We will also conduct a per protocol sensitivity analysis: when clinicians in the usual care group view EEG data, these patients will be included in the guided group; and where there are technical difficulties in viewing electroencephalogram data in the guided group, these patients will be included in the blinded group. Patients who cannot be assessed for delirium will be excluded from the primary outcome analysis. In two sensitivity analyses, these patients (unless they die during surgery) will either all be assumed to have had incident delirium or not to have had incident delirium. We will compare preoperative characteristics between respondents and alive non-respondents to 30-day postoperative surveys. We will do the same for the 1-year postoperative surveys. Results will be presented with 95% CIs. All significance testing will be two-sided, with P values <0.05 considered as providing suggestive evidence and P values <0.005 as providing more compelling evidence
^
56
^. The statistical analyses will be performed with
SAS, V.9.4 (SAS Institute, Cary, North Carolina) and/or
STATA, V.14.2 (StataCorp LP, College Station, Texas).

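### The analysis labelled per protocol is an unadjusted as-treated comparison: it moves patients to the other arm according to whether the EEG was visible

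*Protocol article*

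**What the plan says.** The section 'Sample size calculation statistical analyses' of the protocol article sets the main approach: "Patients will be assessed based on their randomization group in accordance with an intention-to-treat approach". It then continues: "We will also conduct a per protocol sensitivity analysis". Two rules define that analysis. For usual care, "when clinicians in the usual care group view EEG data, these patients will be included in the guided group". For the guided arm, "where there are technical difficulties in viewing electroencephalogram data in the guided group, these patients will be included in the blinded group". The blinded group here is usual care, where the anesthesia team cannot see the EEG.

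Three statements elsewhere bear on these rules:

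- 'Protocol for EEG-guided anesthesia': "In the usual care group, the EEG monitor values are masked from the anesthesia team", signal quality measures excepted.
- The same section says that the guidance protocol "is suggestive and not prescriptive". Its main trigger for reducing anesthetic is EEG suppression, and its second is a low index value.
- 'Randomization and blinding': "The anesthesiologist and the team caring for the patient intraoperatively are not blinded to the group assignment".

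The sample size section lists baseline covariates for an adjusted analysis of delirium, but does not say that this adjustment applies to the per-protocol analysis.

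**The concern.** A per-protocol analysis keeps each patient in the randomised arm and leaves out those who departed from the protocol. The rule here leaves nobody out. It counts departures in the opposite arm, which is an as-treated analysis. Three consequences follow.

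1. The groups compared are no longer those that randomisation formed. Whether a usual-care clinician views a masked EEG is settled after allocation, by a team that knows the allocation. If viewing is related to the patient's risk of delirium, the comparison is confounded. Technical failure in the guided arm is more plausibly unrelated to risk, so the two movements need not cancel.
2. The rule measures visibility, not adherence. A guided patient whose EEG was visible but not acted on still counts as managed per protocol. A usual-care patient whose EEG was seen counts as guided whatever was done with the information.
3. The article applies its P value thresholds of 0.05 (suggestive) and 0.005 (more compelling) to all significance tests. Nothing sets this analysis apart, so its result could be read on that scale as the effect in patients treated as intended.

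**Working it through.** **Reading the rule.** Both clauses place the patient in the other group and neither removes anyone. That settles the classification as as-treated without arithmetic. The arithmetic below shows only how far such a rule can move the result.

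**Inputs from the protocol article.** 1200 patients, allocated 1:1, so 600 per arm; control delirium 25%; planned absolute reduction 8 points, so 17% in the guided arm.

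**The plan's own figure (context only).** Power, normal approximation with pooled variance under the null, mean proportion 0.21:

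- Null SE = √(2 × 0.21 × 0.79 / 600) = 0.0235. Alternative SE = √((0.25 × 0.75 + 0.17 × 0.83) / 600) = 0.0234.
- Two-sided alpha 0.05: (0.08 − 1.96 × 0.0235) / 0.0234 ≈ 1.45, power 92.6%.
- Two-sided alpha 0.005: (0.08 − 2.807 × 0.0235) / 0.0234 ≈ 0.60, power 72.5%.

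The stated bounds of more than 90% and more than 70% reproduce. Nothing below depends on them.

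**Assumed inputs (not in the article).** A share x of each arm crosses over. Delirium risk is rU among patients moved out of usual care and rG among those moved out of the guided arm. The article gives none of these.

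**Formula.** With equal shares moved, both groups stay at 600:

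- usual care as analysed = pU − x·rU + x·rG
- guided as analysed = pG − x·rG + x·rU
- difference (usual care minus guided) = (pU − pG) + 2x(rG − rU)

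The shift away from the intention-to-treat difference is therefore 2x(rG − rU).

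| x each way | rU | rG | As analysed, 25% in both arms | Difference | Difference if the arms are 25% and 17% |
|---|---|---|---|---|---|
| 5% | 40% | 25% | 24.25% vs 25.75% | −1.5 | 6.5 |
| 5% | 25% | 40% | 25.75% vs 24.25% | +1.5 | 9.5 |
| 10% | 40% | 25% | 23.5% vs 26.5% | −3.0 | 5.0 |
| 10% | 25% | 40% | 26.5% vs 23.5% | +3.0 | 11.0 |
| 5% | 40% | 40% | 25% vs 25% | 0 | 8.0 |

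Positive values favour the guided arm. The sign and size depend wholly on who crosses over.

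**Would excluding the same patients cure it?** Take x = 10%, rU = 40%, rG = 25% and no true effect. Usual care becomes (25 − 4)/0.90 = 23.3% and guided (25 − 2.5)/0.90 = 25.0%. The shift is 1.7 points, compared with 3.0 under reassignment. Exclusion reduces the artefact but does not remove it.

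**Complier-average effect.** This is the intention-to-treat risk difference divided by the difference between arms in the proportion managed with visible EEG. If, as an assumption, visibility were 95% and 5%, the divisor is 0.95 − 0.05 = 0.90. The estimate and its interval then scale by 1/0.90 = 1.11, and an 8-point difference becomes 8.9 points.

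**The case against.** The strongest reply is that nothing decisive rests on this analysis. Intention to treat comes first, this is called a sensitivity analysis, and both reassignments are spelled out next to the label, so a careful reader can see who is moved. Because the guidance is only suggestive, EEG visibility is also a defensible, if imperfect, marker of exposure. All of that stands, and it limits the importance of the point. It does not make the label correct or the comparison randomised.

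Several stronger readings are tempting, and the article does not support them:

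- A reader might infer that usual-care clinicians look at the EEG because they are worried about the patient, so that confounding by indication is certain. The article gives no reason for viewing, and accidental unmasking is equally possible. The comparison may be confounded; the text does not show that it is.
- A reader might infer that unmasked usual-care patients received no EEG-based reduction of anesthetic. The article does not say so. A trained clinician who sees suppression may act on it. Viewing simply does not establish whether guidance was followed.
- A reader might move patients only from usual care to guided and obtain a larger artefact. For example, 60 usual-care patients at 50% risk give (150 − 30)/540 = 22.2% vs (150 + 30)/660 = 27.3%, or 5.1 points. That needs 10% crossover in one direction at twice the base risk, and it ignores the reverse move that the same sentence prescribes.

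The remedies have limits too. Exclusion after randomisation can bias. A complier estimate based on visibility uses the same imperfect exposure marker, so it must be described as the effect of management with visible EEG, not of following the guidance.

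**Conclusion.** The point holds as a matter of definition. The analysis is as-treated, unadjusted as stated, and does not estimate what its label says. Its possible bias runs in either direction: 1.5 points at 5% crossover each way and 3.0 points at 10%, with movers' risks of 40% and 25%. It is zero when movers are balanced in number and risk. These figures rest on assumed crossover rates and risks. Against a planned effect of 8 points they are large enough to colour interpretation if crossover is not rare.

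A reader might infer that the trial's main result is compromised. It is not: the intention-to-treat primary comparison, the sample size and the type I error are untouched. This should be corrected, but it does not threaten the trial's main conclusion.

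**What to change.** 1. Rename the analysis as-treated. State that its groups are defined by events after randomisation, that it may be confounded for that reason, and that it carries no confirmatory weight.
2. Adjust it for the baseline covariates already listed in the sample size section (age, sex, history of depression, history of delirium, the two cognitive screens, comorbidity index and center). Note that baseline adjustment cannot remove selection driven by intraoperative events.
3. Add, as the main adherence analysis, a complier-average causal effect that keeps the randomised arms: the risk difference divided by the between-arm difference in the proportion managed with visible EEG. State its assumptions: allocation affects delirium only through EEG visibility, and there are no defiers. The first deserves comment, since the team knows the allocation and might alter management in a guided patient even when the EEG cannot be seen.
4. A per-protocol set that excludes deviators from their randomised arm may be shown as supportive only, because that exclusion can also bias.

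The cost is a change of wording and a few lines of code. No data are needed beyond the record of EEG visibility that the present rule already requires. The drawback is a somewhat wider interval for the complier estimate, about 11% wider at the assumed visibility of 95% and 5%.

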### Postoperative delirium

The primary outcome of the study is the incidence of postoperative delirium. Assessment of postoperative delirium is conducted in patients that can be sufficiently aroused according to a Richmond Agitation and Sedation Score ≥ -3. Assessment of patients for delirium is performed from day one to day 5, once daily, in the afternoon/evening. A diagnosis of delirium for each patient is based on an approach combining a standardized daily assessment with a structured chart review. Members of the research team who are blinded to the treatment arm of the study assess patients for delirium using the Confusion Assessment Method (CAM long form)
^
42
^, or the Confusion Assessment Method for the Intensive Care Unit (CAM-ICU)
^
43,
44
^ for patients who are unable to speak (e.g., have a tracheal tube or tracheostomy). The CAM long form is deemed a viable tool that can be used by non-psychiatrists and by non-mental health professionals for delirium detection
^
42
^. The CAM long form has subsequently been validated in a number of studies and against a reference standard, with a sensitivity of >94% and a specificity of >89%
^
45
^. The CAM long form and the CAM-ICU are reliable instruments in good agreement with the DSM-IV criteria for delirium
^
44,
46,
47
^. To complete the delirium assessment of patients, a trained clinical researcher blinded to the CAM results and group assignment conducts a structured chart reviews for delirium detection. A positive CAM long form, or CAM-ICU, or chart review delirium detection
^
48,
49
^ is deemed sufficient and necessary to diagnose incident delirium in the ENGAGES-Canada trial. The approach combining a CAM long form interview, or a CAM-ICU, plus a chart review results in an increase in the sensitivity while retaining specificity in detecting incident delirium
^
48,
49
^. In addition, use of a chart review bolsters the pragmatic aspects of this trial, since it obtains information from a readily available source. Determination of delirium severity is based on the CAM-S long form measure or the CAM-ICU-7 Delirium severity instrument
^
50,
51
^.

The CAM long form assessment that is used in the trial was developed by [name] and colleagues
^
42

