### Sample size calculation statistical analyses

Based on previous studies in cardiac surgery patients, we conservatively estimated a delirium incidence in the control group of 25%
^
2–
9
^ and based on meta-analyses of randomized trials we estimated a relative reduction in delirium with guidance of anesthesia based on EEG waveform of more than one-third
^
3,
7,
24
^. Assuming a two-sided alpha <0.05 and 1200 patients, we estimated >90% power to be able to detect an absolute decrease in the incidence of delirium of 8%
^
27
^. With a more stringent two-sided alpha <0.005, we estimated >70% power. We anticipate that most patients will be available for primary outcome ascertainment (i.e. incident postoperative delirium assessment). Continuous variables will be presented as mean (SD) or median (interquartile range [IQR]), depending on their distributions. Chi-square or Fisher’s exact tests will be used for comparisons of discrete data. Unpaired Student’s t or Mann–Whitney U tests will be used for comparisons of continuous data, depending on their distributions. Confidence intervals for median differences will be calculated using Hodges-Lehmann estimates, and for differences between proportions we will use Newcombe’s method with continuity correction
^
53
^. For the primary outcome, the proportion of patients with incident postoperative delirium will be compared between the two study groups. We will conduct three post-hoc sensitivity analyses to assess whether improved clinician fidelity to the guided protocol might alter the primary outcome. Within the guided group 25% of cases will be excluded with the (1) longest cumulative electroencephalogram suppression time; (2) longest cumulative time with BIS, WAVcns <40 or PSi <25; and (3) highest median volatile anesthetic concentrations. To compare time to delirium onset between groups, we will construct Kaplan-Meier curves for each group and conduct a log-rank test. We will perform a covariate adjustment including likely risk factors for delirium (including age, sex, history of depression, history of delirium, AD* Test, Short Blessed Test, comorbidity index, and study center) using two methods: (1) logistic regression and (2) standardized estimator combined with bootstrapped 95% confidence intervals (CIs)
^
54
^. We will compare delirium incidence between groups, segregated by Charlson Comorbidity Index categories
^
55

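### The two missing-outcome sensitivity analyses apply the same assumption to both arms, so they respond to imbalance in the number missing but not to different delirium rates among the missing

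*Protocol article*

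**What the plan says.** In the Sample size calculation statistical analyses section, the protocol article sets a complete-case primary analysis: "Patients who cannot be assessed for delirium will be excluded from the primary outcome analysis". Two sensitivity analyses follow. In them these patients, other than those who die during surgery, "will either all be assumed to have had incident delirium or not to have had incident delirium". Nothing in the sentence separates the arms, so the plain reading is one common value for both. The article states no other analysis of missing primary outcomes. It gives no expected missing rate and says only that most patients should be available.

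The Postoperative delirium section says that assessment is "conducted in patients that can be sufficiently aroused according to a Richmond Agitation and Sedation Score" of −3 or higher. It also says that a positive chart review alone is enough to diagnose delirium.

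Results are read against two thresholds: P<0.05 is suggestive evidence and P<0.005 is more compelling evidence.

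**The concern.** A check on excluded patients should show how different from the observed patients they would have to be before the conclusion changed. What threatens a treatment comparison is missing patients in the two arms having different delirium rates. Both planned analyses set those rates equal, at 100% in both arms or 0% in both arms, so neither looks at that possibility.

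Such a difference is conceivable here. Interview assessment depends on arousal, the intervention alters anesthetic exposure, and the outcome is a disorder of the brain. If the missing counts turned out similar, the report could present two agreeing sensitivity analyses as evidence that the exclusion did not matter, although their agreement would follow from arithmetic. A result near either evidence threshold would be the most exposed.

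**Working it through.** **Inputs from the article.** Control incidence: "we conservatively estimated a delirium incidence in the control group of 25"%. Effect: "to be able to detect an absolute decrease in the incidence of delirium of 8"%, so 25% vs 17%. Size and power: "Assuming a two-sided alpha <0.05 and 1200 patients, we estimated >90% power"; "With a more stringent two-sided alpha <0.005, we estimated >70% power". Allocation is 1:1, so 600 per arm.

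**Assumed, because the article gives no figure.** Missing 2%, 5% or 10% per arm when balanced. When unbalanced: 3% usual care vs 5% guided, 2% vs 8%, and 8% vs 2%.

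**Step 1: reproduce the stated power.** Pooled normal approximation, mean rate 0.21:

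- Standard error under no difference: √(2×0.21×0.79/600) = 0.02352.
- Standard error under the alternative: √((0.25×0.75 + 0.17×0.83)/600) = 0.02340.
- Alpha 0.05: (0.08 − 1.960×0.02352)/0.02340 = 1.45, power 92.6%.
- Alpha 0.005: (0.08 − 2.807×0.02352)/0.02340 = 0.60, power 72.5%.

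Both stated figures hold.

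**Step 2: the general formula.** Let pU and pG be the observed delirium rates (usual care, guided), mU and mG the missing shares, and qU and qG the delirium rates among the missing. The reduction with guidance is

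D = pU(1−mU) − pG(1−mG) + qU·mU − qG·mG.

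The planned analyses are qU=qG=1 and qU=qG=0. If mU=mG=m, then

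D = (1−m)(pU−pG) + m(qU−qG).

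Whenever qU=qG the last term is zero, so both planned analyses give (1−m)(pU−pG). The opposite-arm extremes shift this by −m or +m.

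**Step 3: balanced missingness, whole-patient counts, pooled z test.** At 5% missing (30 per arm), complete cases are 142/570 vs 97/570, a difference of 7.9 points.

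- All delirium: 172/600 vs 127/600 = 7.5 points, p=0.0027.
- None delirium: 142/600 vs 97/600 = 7.5 points, p=0.0011.
- Guided missing delirious, usual-care missing not: 142/600 vs 127/600 = 2.5 points, p=0.30.
- The reverse: 172/600 vs 97/600 = 12.5 points.

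| Missing per arm | All delirium | None delirium | Worst bound for guidance | Best bound for guidance |
|---|---|---|---|---|
| 2% | 7.8 (p=0.0012) | 7.8 (p=0.0008) | 5.8 (p=0.014) | 9.8 |
| 5% | 7.5 (p=0.0027) | 7.5 (p=0.0011) | 2.5 (p=0.30) | 12.5 |
| 10% | 7.2 (p=0.0062) | 7.2 (p=0.0015) | −2.8 (p=0.25) | 17.2 |

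**Step 4: less extreme cases at 5% missing per arm.** Take 25% delirium among missing usual-care patients (7.5 of 30).

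- 50% among missing guided patients (15 of 30): 149.5/600 vs 112/600 = 6.25 points, p=0.009.
- 75% among missing guided patients (22.5 of 30): 149.5/600 vs 119.5/600 = 5.0 points, p=0.038.

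Both lose the 0.005 threshold. The planned pair shows neither.

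**Step 5: unbalanced missingness (usual care / guided).**

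- 3% / 5%: all delirium 6.2 points (p=0.013); none 8.2 points.
- 2% / 8%: all delirium 2.8 points (p=0.26); none 8.8 points.
- 8% / 2%: all delirium 12.3 points; none 6.3 points (p=0.0059).

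Here the planned pair does move, by roughly the difference in missing shares.

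**The case against.** A reader might infer that the planned pair can never fail and that the result will always look robust. The documents do not support that. The sentence on missing patients fixes their values, not their numbers. With unequal numbers the pair can overturn the result, as the 2% / 8% case shows. Even with 10% missing in each arm, the all-delirium analysis gives p=0.0062 and crosses the article's own 0.005 line. If being unassessable depends on the arm, unequal counts are a likely consequence, and the plan would then pick up part of the problem.

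A reader might also infer that the arousal threshold makes many outcomes missing. The article points the other way. Patients are assessed daily on days 1 to 5, so one day of deep sedation does not by itself lose the outcome. Chart review can establish delirium without an interview, and the Strengths of the study and limitations section says that it also limits missing outcomes. That section expects the vast majority of patients to be extubated within 48 hours. Missingness may therefore be low.

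The opposite-arm extremes assume 100% delirium in one arm's missing patients and 0% in the other's, so they are bounds rather than likely scenarios. Grid detail often belongs in an analysis plan, which is not shown here.

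These points limit the size of the concern but do not remove it. The article itself fixes the exclusion and the content of the two checks. Similar missing counts are an ordinary outcome under 1:1 allocation, and in that case the pair says nothing about different delirium rates among the missing. The less extreme cases at 5% missing show that the bounds are not needed to change the reading.

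**Conclusion.** The point holds in limited form. The two stated analyses test sensitivity to how many patients are missing in each arm, not to how delirium differs among them. With similar missing counts they shrink the difference by the factor (1−m) and do nothing else.

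How much this matters depends on a missing rate that the article does not give. At the design effect and an assumed 5% per arm, both planned analyses stay below 0.005 while the opposite-arm range is 2.5 to 12.5 points, and significance is lost at the lower end. At an assumed 2% the conclusion at 0.05 survives the worst bound. At an assumed 10% that bound changes sign (−2.8 points, p=0.25).

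The documents do not show that the primary result will be biased, or that missingness will be large or will differ by arm. The conclusion is that the stated checks would not reveal arm-specific differences among the missing if these occurred.

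**What to change.** Keep the two planned analyses. Before unblinding, add a tipping-point grid that varies the delirium rate among missing patients separately in each arm, with the two opposite-arm extremes as its outer bounds. Report where on the grid P passes 0.05 and 0.005, so that readers can judge whether those combinations are plausible. Report the number missing in each arm, with intraoperative deaths shown separately because the planned analyses leave them out.

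The cost is a little more analysis and one more table or figure. The extremes should be labelled as bounds, so that they are not read as expected results.
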